#### Outcome measures

Service-level and individual-level outcomes will be examined to explore how these vary within and between reablement service type and by individual characteristics.

#### Individual participant level outcomes

Outcome measures have been selected which together capture health, well-being, social inclusion, participation and self-efficacy. In addition, attainment of user-specific reablement goals will be recorded.

#### Primary outcome measure

The EQ-5D-5L questionnaire will be the primary outcome measure used to measure health-related quality of life [24, 25]. It represents five dimensions of quality of life: mobility, self-care, usual activities, pain/discomfort and anxiety/depression. Respondents indicate the level of difficulty they are experiencing in each of these domains on a five point scale (no problems, some problems, moderate problems, severe problems, unable).

#### Secondary outcome measures

The Adult Social Care Outcomes Toolkit (ASCOT SCT-4) [26, 27] will be used to measure social-care related quality of life. It measures social care quality of life across nine domains: control over daily life; personal cleanliness and comfort; food and drink; personal safety; social participation and involvement; occupation; accommodation cleanliness and comfort; dignity. The ASCOT tools are used routinely by local authorities and government and were used in a previous national evaluation of reablement services in England [11].

#### General health questionnaire (GHQ-12)

The GHQ-12 is a measure of current mental health [28]. It focuses on two major areas—the inability to carry out normal functions and the appearance of new and distressing experiences. It is well suited for longer-term studies that require an indicator of minor psychiatric morbidity [29].

#### User-defined goal attainment

It is routine practice for quantifiable reablement goals to be agreed between practitioners and individuals when the reablement assessment process takes place [11]. We will record the goals set with each participant and determine goal attainment as per the service method when the participant is discharged from the service.

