The UK government has invested substantially in reablement services as there is some evidence that they can enhance independence and have the potential to contain costs [11]. This was signalled by £70 million extra funding made available to the UK National Health Service (NHS) in 2010 to support hospital discharge [12], followed by £300 million/year over 2012–15 for ‘reablement spending’ [13]. More recently, the UK government announced an investment of £91.6 billion in local NHS services in 2012/3, including £150 million for reablement [14]. The promotion of reablement services within the Care and Support 2012 White Paper has also firmly established it as a priority for local authorities [15].

While existing research suggests that reablement can lead to improvements in health-related quality of life, social care outcomes and physical functioning and remove or decrease the need for commissioned health and home care services [11, 16], the evidence base around reablement services remains limited and significant questions remain. The rapid development of reablement services in England (UK) has created variation in the service landscape. Differences in how services are funded and delivered by different organisations and their effectiveness on service user outcomes cannot be addressed by the existing body of research in this area [11]. Reablement is reported to work differently for different people, being less effective for those with chronic/complex health problems compared to people recovering from acute illnesses or falls [17]. Considerable variation is also reported in local arrangements for self-care services for long-term conditions [18]. Indeed, for some groups (e.g. young adults with life-limiting conditions and adults with dementia), the evidence base is virtually non-existent. Evidence suggests that the number and proportion of people with specialist needs is growing fast. For example, the number of people living with dementia in the UK is expected to double in the next 30 years while the overall costs of dementia in the UK are estimated to triple from £17 billion per year to over £50 billion [19]. The rapid rise in the number and proportion of people with specialist needs suggests that responding to such needs will become an ever-growing pressure on health and social care services. It is, therefore, important that both those populations that access ‘generic’ reablement services as well as those with specialist needs are represented in this research.

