### Outcomes evaluation (WP2a)

WP2a outcomes evaluation is a quantitative evaluation of the effectiveness of the different service types, which will examine short and longer-term service-level and individual-level outcomes, and compare outcomes between service types. Quantitative patient-reported and practitioner-reported measures will be used to understand the effects of reablement and the impact of service and user characteristics and other factors on effectiveness.

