#### Sample size

The statistical approaches chosen to measure outcomes takes into account the potentially clustered nature of the data collected.

The marginal effect of reablement versus home care as usual in a previous prospective longitudinal study was 0.107 [11]. This was taken as comparable to Cohen’s f^2^ [31] and indicative of a small to medium effect size. It was assumed that differences in effect size between different types are likely to be smaller than those seen between reablement versus usual care and have, therefore, used the relatively small effect size of f^2^ = 0.06. Using a sample size calculation for hierarchical multiple regression, without clustering, the minimum total sample size required to detect an effect size of 0.06 with a power of 80 % and an alpha of 0.05, and with up to twenty individual predictors and four reablement service type predictors would be 222.

In order to account for clustering in the sample size calculations, two reported estimates of intra-class correlations (ICC) and the associated design effects have been used [32]: i) a reported ICC of 0.007 for overall health with an average cluster sample size of 200; this would result in a design effect of 2.393; and ii) the highest reported ICC of 0.01355 in the study [32]. This was deemed necessary for the sample size estimate as people eligible for reablement are likely, as a group, to display less variation in overall health (and therefore a higher ICC). The ICC of 0.01355 was rounded to 0.014 and, using an average cluster size as above, results in a design effect of 3.786.

Inflated by the two design effects given above (2.393 and 3.786), the study will need to achieve a sample size of between 532 and 841. Assuming an attrition rate of 25 % between T_0_ and T_2_, the study will need to recruit between 710 and 1121 people in total. A pragmatic decision was made to recruit between these two figures, giving a sample of 800 people in total, around 200 per each of the four reablement service types to be evaluated in WP2.

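### Goal attainment follows each service's own scoring method, so a difference between service types on this non-primary outcome may reflect scoring or goal difficulty

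*Protocol article*

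**What the plan says.** Under *Individual participant level outcomes* (WP2a), the protocol article adds to the chosen questionnaires that "attainment of user-specific reablement goals will be recorded". Under *User-defined goal attainment* it explains how goals arise: "It is routine practice for quantifiable reablement goals to be agreed between practitioners and individuals". The study will record each participant's goals and "determine goal attainment as per the service method when the participant is discharged from the service".

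The use of these data is set in two other places. *Outcomes evaluation (WP2a)* says that the work package will "compare outcomes between service types". *Outcome measures* says that service-level and individual-level outcomes will be examined to "explore how these vary within and between reablement service type and by individual characteristics".

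The article gives no common attainment scale, no threshold for calling a goal met, no independent rating and no mapping from local ratings to a study variable.

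**The concern.** The comparison runs across services, while the yardstick is whatever each service uses. If one service counts partly met goals as attained and another requires every goal to be met in full, their attainment figures differ even when their users have done equally well. The *Background* section gives a reason to take this seriously: "The rapid development of reablement services in England (UK) has created variation in the service landscape".

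Goal difficulty adds a second problem. Goals are agreed locally between practitioner and user, so a service that sets modest goals can show higher attainment without achieving more.

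At stake is the one outcome framed in the user's own terms. A commissioner could read higher attainment in one service type as greater effectiveness when it shows only a more lenient rule or easier goals.

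**Working it through.** **1. Can the planned analysis separate scoring from service type?** The *Analysis* section for WP2a plans multilevel modelling of user characteristics, service type and time. A scoring rule is a property of the service, not of the user, so user covariates do not absorb it. *Sample size* assumes an average cluster of 200 and around 200 people per service type. That implies 200 / 200 = about one cluster per type, although the number of sites per type is not stated. With one cluster per type, scoring method and service type coincide and a site effect cannot separate them. With several sites per type, differing rules would add noise and possibly bias.

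**2. The plan's own figures.** The article gives no figure for goal attainment. The sample size rests on "the relatively small effect size of f^2^ = 0.06" and does not concern this outcome. Its design effects are used below, so they are checked first with DE = 1 + (m − 1) × ICC:

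- 1 + 199 × 0.007 = 2.393, as stated
- 1 + 199 × 0.014 = 3.786, as stated

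**3. Inputs to the illustration.**

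- From the article: about 200 users per type; 25% attrition, so 200 × 0.75 = 150; alpha 0.05, taken here as two-sided; ICC 0.007 and 0.014.
- Assumed: true attainment 60% in both of two types; one service's rule adds 10 or 15 points; the article's ICCs, which were reported for overall health, also apply to goal attainment.

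**4. Formula.** The probability that a two-proportion test declares a difference is Φ[(d − 1.96 × SE0) / SE1], where d = p2 − p1, SE0 = √(2 p̄(1 − p̄)/n) and SE1 = √((p1(1 − p1) + p2(1 − p2))/n). For clustering, n is replaced by n / DE with m = n.

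Example for n = 200 and 0.60 against 0.70:

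- SE0 = √(0.455/200) = 0.0477
- SE1 = √(0.45/200) = 0.0474
- (0.10 − 1.96 × 0.0477) / 0.0474 ≈ 0.14, and Φ gives 0.555

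The same case with n = 200 / 3.786 = 52.8 has SE0 = 0.0928 and SE1 = 0.0923, and gives 0.187.

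| n per type | DE | Effective n | 10-point shift | 15-point shift |
|---|---|---|---|---|
| 150 | none | 150 | 0.442 | 0.795 |
| 200 | none | 200 | 0.555 | 0.896 |
| 150 | 1 + 149 × 0.007 = 2.043 | 73.4 | 0.244 | 0.492 |
| 200 | 2.393 | 83.6 | 0.272 | 0.544 |
| 150 | 1 + 149 × 0.014 = 3.086 | 48.6 | 0.176 | 0.350 |
| 200 | 3.786 | 52.8 | 0.187 | 0.375 |

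Using SE1 in place of SE0 moves these values by about one point at most. The ranges are then about 44–56% and 80–90% without clustering, and 18–27% and 35–55% with it. A 5-point shift gives about 14–18% and 7–10%.

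**5. Could a shift of this size arise?** Suppose every user has k = 3 or 4 goals, each met with the same probability p in every service (assumed 0.6 to 0.8). A rule requiring all goals gives p^k, from 0.6^4 = 0.13 to 0.8^3 = 0.51. A rule requiring most goals gives, for k = 3 and p = 0.6, 3 × 0.36 × 0.4 + 0.216 = 0.648, and from 0.48 to 0.90 over the same range. Two reasonable rules can thus differ by much more than 15 points on identical performance.

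**The case against.** - **The methods may not differ.** The article nowhere says that services score goals differently. The variation described in the *Background* concerns how services are funded and delivered. A reader might infer that the instrument does vary with service type; the text supports only that it may, and that nothing prevents it.
- **Who judges is not stated.** A reader might infer that each service marks its own work. The article says that the study team determines attainment by the service's method, and does not say who makes each judgement. The supported point is about the rule, not the rater.
- **The outcome is peripheral.** EQ-5D-5L is primary; ASCOT SCT-4 and GHQ-12 are common instruments. The wording on variation between types is exploratory, and no specific test of goal attainment is named. One concrete use, choosing interviewees by level of goal achievement in the process evaluation, is well served by a local rating. This stands, and it limits the importance of the point.
- **The unclustered rates overstate.** Quoting only 44–56% or 80–90% would ignore the clustering that the article plans for. The clustered rates are lower but still well above 5%. The 60% base and the sizes of the shifts have no anchor in the article. The figure of 150 also borrows attrition up to six months after discharge, while attainment is fixed at discharge.
- **An article condenses.** A fuller protocol might map local ratings to one variable. But the article states a measurement rule rather than leaving one out, and a later analysis plan cannot make ratings comparable if they were collected only under different rules.

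**Conclusion.** The point holds as a risk built into a stated measurement rule. Goal attainment is scored by the service's method, individual outcomes are to be compared between service types, and no common scale links the two. A difference between types could then be due to scoring or to goal difficulty, and adjustment for user characteristics would not reveal which.

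The size cannot be derived from the article. Under the assumptions above, false significance occurs in about 18–27% of studies for a 10-point scoring shift and 35–55% for a 15-point shift once n is deflated for the article's ICCs, against a nominal 5%. If the methods happen to agree, the scoring part vanishes and only goal difficulty remains.

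A reader might conclude that any observed difference would be a pure artefact, or that the WP2a comparison as a whole is compromised. The article supports neither. The problem is confined to this one non-primary outcome, and the service's own rating remains usable within a service.

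**What to change.** In *User-defined goal attainment*, add one common rating of each recorded goal at discharge, for example met / partly met / not met, under one written study rule. It can sit with the engagement measure that practitioners already complete at T1 (*Engagement in reablement*). The rating must be made at discharge, because the recorded goals alone do not show whether they were reached.

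Use the common rating for any comparison between service types. State alongside it that goal difficulty may still differ between services, since a common scale does not correct for that. Keep the service's own rating for description within services and for selecting interviewees. If no common rating is collected, state that goal attainment will not be compared between types.

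The cost is one extra discharge item, a short scoring rule and a little coding work.

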#### Service level outcomes

The reason for referring an individual to a reablement service can be conceived as falling into one of two broad categories: to support an individual to return home (RH) from hospital or residential care setting following an acute episode or to support an individual to remain at home (RAH). Service level outcomes will include the proportion of RH users readmitted to hospital within six months of discharge from the reablement service; the proportion of RAH service users placed in residential care within six months of discharge from the reablement service; and the proportion of RAH service users with reduced use of ‘home care’ type services at six months after discharge from the reablement service.

#### Other measures

##### Experiences of reablement practice

At discharge (T_1_), research participants will complete a brief questionnaire about their views on the practice and approach of the reablement practitioners who worked with them. This will cover their perceptions of their relationship with reablement practitioners and their views on the way practitioners worked with them. There are no pre-existing questionnaires or measures which captures this concept, therefore the research team will develop and pilot a questionnaire in Year 1 of the study.

##### Engagement in reablement

At discharge (T_1_), reablement practitioners will complete a measure of user engagement in reablement. There are no pre-existing measures of engagement in reablement and therefore the Hopkins Rehabilitation Engagement Rating Scale (HRERS) will be adapted for this study with permission from the authors [30]. The HRERS was developed to measure service user engagement in acute rehabilitation services. Some adaptations are required to make it suitable for use in a reablement context. Specifically, the word ‘therapy’ will need to be replaced with a suitable alternative and the first item concerns attendance rates at outpatient clinics, so these will need to be adapted to reflect delivery of reablement services in the client’s home. During Year 1 of the study a consultation will be undertaken with rehabilitation practitioners regarding adaptations.

#### Sample size

The statistical approaches chosen to measure outcomes takes into account the potentially clustered nature of the data collected.

The marginal effect of reablement versus home care as usual in a previous prospective longitudinal study was 0.107 [11]. This was taken as comparable to Cohen’s f^2^ [31] and indicative of a small to medium effect size. It was assumed that differences in effect size between different types are likely to be smaller than those seen between reablement versus usual care and have, therefore, used the relatively small effect size of f^2^ = 0.06. Using a sample size calculation for hierarchical multiple regression, without clustering, the minimum total sample size required to detect an effect size of 0.06 with a power of 80 % and an alpha of 0.05, and with up to twenty individual predictors and four reablement service type predictors would be 222.

In order to account for clustering in the sample size calculations, two reported estimates of intra-class correlations (ICC) and the associated design effects have been used [32]: i) a reported ICC of 0.007 for overall health with an average cluster sample size of 200; this would result in a design effect of 2.393; and ii) the highest reported ICC of 0.01355 in the study [32]. This was deemed necessary for the sample size estimate as people eligible for reablement are likely, as a group, to display less variation in overall health (and therefore a higher ICC). The ICC of 0.01355 was rounded to 0.014 and, using an average cluster size as above, results in a design effect of 3.786.

Inflated by the two design effects given above (2.393 and 3.786), the study will need to achieve a sample size of between 532 and 841. Assuming an attrition rate of 25 % between T_0_ and T_2_, the study will need to recruit between 710 and 1121 people in total. A pragmatic decision was made to recruit between these two figures, giving a sample of 800 people in total, around 200 per each of the four reablement service types to be evaluated in WP2.

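### The effect size f² = 0.06 is derived by reading a marginal effect of 0.107 as Cohen's f², so 80% power for between-type differences smaller than the reablement effect is not shown

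*Protocol article*

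**What the plan says.** All of this is in the Sample size section for the outcomes evaluation (WP2a) of the protocol article.

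- Starting figure: "The marginal effect of reablement versus home care as usual in a previous prospective longitudinal study was 0.107 [11"]. The outcome, its unit, its SD and the group sizes are not given.
- Interpretation: "This was taken as comparable to Cohen’s f^2^ [31] and indicative of a small to medium effect size".
- Reasoning: the section assumes that "differences in effect size between different types are likely to be smaller than those seen between reablement versus usual care", and on that ground "used the relatively small effect size of f^2^ = 0.06".
- Calculation: hierarchical multiple regression "with a power of 80 % and an alpha of 0.05", and the total without clustering "with up to twenty individual predictors and four reablement service type predictors would be 222".
- Clustering: design effects of 2.393 (ICC 0.007) and 3.786 (ICC 0.014), both with clusters of 200, raise this to 532–841. Allowing for 25% attrition gives 710–1121.
- Target: 800, chosen between those two limits, about 200 per service type.

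The primary outcome is the EQ-5D-5L. The article gives no SD and no target difference for it.

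**The concern.** The step from 0.107 to 0.06 compares two different kinds of quantity. The first says how far apart two groups are, in units of the outcome. The second says how much variance a set of predictors explains relative to what remains. That 0.06 is the lower number does not make it the smaller effect.

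Comparing service types is the main purpose of the study, and the results are meant to guide commissioners. A reader of this section would take it that the study has 80% power for differences smaller than the effect of reablement over usual home care. If that is not so, a non-significant service-type effect could be taken as evidence that service type does not matter, when the study had little chance of showing a difference of that size.

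**Working it through.** **1. The plan's own chain, taking f² = 0.06 as given.** Inputs from the section: 4 tested predictors (u = 4), 24 in total, alpha 0.05, power 80%. The test is the F test of the R² increment, with v = N − 25 and noncentrality λ = f²(u + v + 1).

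- Power at N = 222 is 79.6%, and N = 224 is the first to reach 80%. The stated 222 reproduces.
- Design effects: 1 + 199 × 0.007 = 2.393 and 1 + 199 × 0.014 = 3.786.
- 222 × 2.393 = 531.2, so 532. 222 × 3.786 = 840.5, so 841.
- 532/0.75 = 709.3, so 710. 841/0.75 = 1121.3, given as 1121.

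The arithmetic after f² = 0.06 is sound. The question is where 0.06 comes from.

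**2. What the conversion needs.** For two groups in proportions p and 1 − p, a difference D has f² = p(1 − p)(D/SD)², where SD is the residual SD. With equal groups this is (D/(2·SD))². The section supplies neither p nor SD.

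*Assumptions, not in the documents:* 0.107 is in EQ-5D index points, groups are equal, and residual SD lies between 0.15 and 0.35.

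- f² = 0.107 requires SD = 0.107/(2√0.107) = 0.164.
- f² = 0.06 requires SD = 0.107/(2√0.06) = 0.218. Above that SD, the whole reablement effect is smaller than f² = 0.06.

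**3. What f² = 0.06 means between four equal-sized types.** With f = √0.06 = 0.245, the best-to-worst gap runs from 2f·SD = 0.49 SD (two types high, two low) to √8·f·SD = 0.69 SD (one high, one low, two in the middle).

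| Residual SD | f² of the whole effect (0.107) | Gap implied by f² = 0.06 |
|---|---|---|
| 0.15 | 0.127 | 0.073–0.104 |
| 0.20 | 0.072 | 0.098–0.139 |
| 0.25 | 0.046 | 0.122–0.173 |
| 0.30 | 0.032 | 0.147–0.208 |
| 0.35 | 0.023 | 0.171–0.242 |

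The gap is below 0.107 under every pattern at SD 0.15. It straddles 0.107 at SD 0.164–0.20, and from about 0.22 it exceeds 0.107 under every pattern.

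**4. Power for a smaller gap.** As an example of a difference smaller than the reablement effect, take half of 0.107, which is 0.0535. The 800 recruited, less 25%, leave 600 analysed. Effective N is 600/2.393 = 251 or 600/3.786 = 158. The f² range is (0.0535/(√8·SD))² to (0.0535/(2·SD))².

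| Residual SD | f² for a gap of 0.0535 | Power, effective N 251 | Power, effective N 158 |
|---|---|---|---|
| 0.15 | 0.016–0.032 | 29–55% | 18–34% |
| 0.20 | 0.009–0.018 | 17–32% | 12–20% |
| 0.25 | 0.006–0.011 | 12–21% | 9–14% |
| 0.30 | 0.004–0.008 | 10–16% | 8–11% |
| 0.35 | 0.003–0.006 | 9–13% | 7–9% |

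**5. Separating out the choice of 800.** With f² = 0.06 accepted in full, 600 analysed give power of about 85% at ICC 0.007 and about 61% at ICC 0.014. The last column of the second table therefore includes a loss that has nothing to do with reading 0.107 as f². The column for effective N 251 does not include it, and it never exceeds 55%.

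**The case against.** The strongest reply is that the 80% is stated for f² = 0.06, not for any EQ-5D difference, and on those terms it reproduces. That stands. A reader might infer that the 80% power calculation is itself wrong. The documents do not support this, because no arithmetic step is in error. Nor does the section claim 80% power for 800 at both ICCs.

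A reader might also infer that f² = 0.06 necessarily implies a gap between types as large as the whole reablement effect, or larger. The documents do not support that either. It needs 0.107 to be in EQ-5D points, equal groups and a residual SD, and none of these is given. The model allows up to twenty individual predictors, so the residual SD could be low. At 0.15 the implied gap is below 0.107 under every pattern, and at 0.164 the reading of 0.107 as f² happens to be numerically right. At 0.20 the whole effect has f² = 0.072, so 0.06 is still the smaller value on the f² scale.

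These points limit what can be said about the direction and size of the error. They do not rescue the equivalence, because the section gives no SD or group split that would place the study in the favourable part of the range.

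**Conclusion.** The point holds as a fault in the sample-size assumption, not in the arithmetic. A marginal effect cannot be read as f² without a residual SD and a group split, so the stated reason for f² = 0.06 fails, and every later figure rests on that value. The 80% power is valid for f² = 0.06. It is not shown for between-type differences that are "likely to be smaller than those seen between reablement versus usual care", which is the case the section says it has in mind.

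On the assumptions above (EQ-5D index points, four equal-sized types, 600 analysed), no residual SD from 0.15 to 0.35 gives 80% power for a gap half of 0.107. Power is about 7–32% at SD 0.20–0.35 and at most 55% at SD 0.15. The half-size gap is an illustration, not a figure from the protocol. The point should be corrected, but it does not invalidate the design.

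**What to change.** In the Sample size section:

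1. Delete the statement that 0.107 is comparable to Cohen's f².
2. State the target between-type difference in EQ-5D-5L index units, with a residual SD and its source, and show the conversion to f², including the assumed pattern of type means.
3. Report the smallest between-type difference that the planned 800 (600 analysed) can detect with 80% power, at each of the two ICCs.
4. Drop the implication that the study is powered for differences smaller than the reablement effect, unless the conversion supports it.

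The cost is a rewording and a short recalculation. Restating the figures needs no extra recruitment. The downside is that the stated power will probably look less favourable.

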#### Analysis

Baseline (T_0_) demographic and social characteristics of participants at each case site will be summarised using descriptive statistics. Categorical data will be reported as counts and percentages. Continuous data will be expressed as mean values with standard deviations, however median and inter quartile range will be reported if the data is skewed. Multilevel modelling has been chosen as the most appropriate analytical approach for this type of study design, which allows exploration of more than one explanatory variable at different levels and facilitates analysis of cross-level interactions [33]. This will allow separate analysis of the impact of service user characteristics, the types of reablement service, and time on service user outcomes, and identification of any possible interactions between them. This approach is thus ideally suited to exploring questions of effectiveness and which sub-groups of service users might benefit most.

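### The cluster size of 200 either means one service per type, so type and service cannot be separated, or it is the wrong cluster size; the number of services per type must be stated

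*Protocol article*

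**What the plan says.** The Sample size section of WP2a plans to "detect an effect size of 0.06 with a power of 80 % and an alpha of 0.05", and reports that the unclustered minimum "with up to twenty individual predictors and four reablement service type predictors would be 222". It then allows for clustering with two intra-class correlations. The lower, 0.007, is applied "with an average cluster sample size of 200; this would result in a design effect of 2.393". For the higher, 0.014, the section says that "using an average cluster size as above, results in a design effect of 3.786". This gives 532 to 841 people, or 710 to 1121 recruited after 25% attrition. A pragmatic total of 800 is chosen, described as "around 200 per each of the four reablement service types to be evaluated in WP2".

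The Analysis section of WP2a chooses multilevel modelling and says of it: "This will allow separate analysis of the impact of service user characteristics, the types of reablement service, and time on service user outcomes".

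The Discussion describes the study as quasi-experimental. No section gives the number of services or sites per type, or requires at least two.

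**The concern.** Service type is a property of the service, not of the person. The effect of type can be told apart from ordinary differences between services only if each type is represented by more than one service. The article uses the same figure, 200, as the cluster size and as the number of people per type. Taken at face value, each type is then one cluster.

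A design effect increases the number of people and adds no services. With one service per type, local differences in staffing, case mix or care market could not be told from an effect of the service model, and there is no randomisation to balance them. Whether service type affects outcomes is a main question of the study, and the results are meant to guide commissioners.

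**Working it through.** **Inputs, all from the WP2a Sample size section:** f² = 0.06; alpha 0.05; power 80%; 24 predictors, of which 4 are for service type; ICC 0.007 and 0.014; cluster size 200; attrition 25%; 800 recruited; four types.

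**Step 1. Reproduce the plan's figures.**
- Unclustered N: F test of R² change with u = 4, v = N − 25 and noncentrality f²(u + v + 1) needs 224. At N = 222 the power is 79.6%. This agrees with the stated 222.
- Design effect = 1 + (m − 1) × ICC: 1 + 199 × 0.007 = 2.393, and 1 + 199 × 0.014 = 3.786. Both are exact.
- 222 × 2.393 = 531.2 and 222 × 3.786 = 840.5, rounded up to 532 and 841.
- 532/0.75 = 709.3 and 841/0.75 = 1121.3, against the stated 710 and 1121.

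The arithmetic is sound. The question is what the 200 stands for.

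**Step 2. Reading A: 200 is this study's cluster size.**
- Clusters: 800/200 = 4, one per type.
- Degrees of freedom for service variation within type: 4 services − 4 types = 0. The indicator matrix for type and service together has rank 4, the same as for type alone.
- Completers: 800 × 0.75 = 600, or 150 per service. In outcome SD units, the standard error of a difference between two service means has a sampling part √(2(1 − ICC)/150) = 0.115 and a between-service part √(2 × ICC) = 0.118 (ICC 0.007) or 0.167 (ICC 0.014). More people per service shrink only the first part.
- If the model has no service term and there is no type effect, the F ratio for type is inflated by (1 + (m − 1) × ICC)/(1 − ICC). With m = 150 this is 2.043/0.993 = 2.06 and 3.086/0.986 = 3.13. The nominal 5% test on 3 and 596 df then rejects 28.3% and 47.4% of the time.

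**Step 3. Reading B: several services per type.**
- Two services of 100 per type give design effects of 1 + 99 × 0.007 = 1.69 and 1 + 99 × 0.014 = 2.39, not 2.393 and 3.786. The ranges 532–841 and 710–1121 therefore do not apply.
- Power for f² = 0.06 with k services per type and 600 completers: m = 150/k, effective N = 600/design effect, noncentrality 0.06 × effective N, F test on 3 and 4(k − 1) df.

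| k | m | Design effect (ICC 0.007 / 0.014) | Effective N | Denominator df | Power |
|---|---|---|---|---|---|
| 1 | 150 | 2.043 / 3.086 | 293.7 / 194.4 | 0 | not testable |
| 2 | 75 | 1.518 / 2.036 | 395.3 / 294.7 | 4 | 70.0% / 57.3% |
| 3 | 50 | 1.343 / 1.686 | 446.8 / 355.9 | 8 | 93.4% / 86.7% |
| 4 | 37.5 | 1.256 / 1.511 | 477.9 / 397.1 | 12 | 97.7% / 94.8% |

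**The case against.** A reader might infer that the study definitely has one service per type and that its primary comparison is therefore confounded. The article does not support that as a statement of fact. One service per type is an inference from two matching figures. The Setting section speaks of services and providers in the plural. The Staff sampling section of the process evaluation allows for more than one commissioner or manager within a type, and says the case sites were still to be confirmed. The Discussion refers to variation between services or sites. The 200 may also be the cluster size in the source of the ICCs, and its match with 800/4 may be coincidence. All of this stands, and it makes the finding conditional. It does not rescue the calculation: a design effect applied to this study's 222 has to use this study's cluster size.

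A reader might also take the 28–47% as the error rate of the planned analysis. That is not supported either. The article proposes a multilevel model and says clustering is taken into account, so the rates apply only with one service per type and no service term. They also use the ICCs unadjusted, and the individual predictors could lower the residual ICC.

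With several services per type, a design effect at 200 overstates the number of people needed, which is conservative. That is true for participants but not for degrees of freedom: with two services per type, power is below 80% at both ICCs.

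Finally, an article may leave site numbers and details of the random effects to a fuller document, and their absence is not the complaint. The complaint is that the stated cluster size, number per type and promised separation of type do not fit together.

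**Conclusion.** The point holds in conditional form: the sample size section does not fit its purpose on either reading.

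- **One service per type.** Type and service are completely confounded, and the separate analysis of service type promised in the Analysis section is not possible. Leaving out the service term would bring false-positive rates of about 28% to 47%.
- **Several services per type.** The design effects and both sample size ranges do not describe the study. Whether the question can be answered then depends on a number the article does not give: power runs from 57–70% with two services per type to 95–98% with four.

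These figures rest on the article's own ICCs, f² = 0.06, 600 completers spread equally over services, and a 3-df test of type. Which reading is right cannot be settled from the article. The matter needs settling before services are recruited, because no later analysis can create between-service degrees of freedom.

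**What to change.** State the number of services per type. Where feasible, keep the total of 800 and spread it over several services per type, preferably at least three. Recompute the design effect and restate power at the actual cluster size. Fit service as a random effect nested in type, and test type against between-service variance with small-sample degrees of freedom (Kenward–Roger or Satterthwaite).

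If only one service per type can be recruited, withdraw the claim about the effectiveness of service types. Report a comparison of four individual services and say that type and site cannot be separated.

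The cost is more service set-ups for the same number of participants; whether that is feasible cannot be judged from the article. The fallback costs only wording and a narrower conclusion.
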